## Abstract

**Introduction:**

Combined treatment using anti‐programmed death‐ligand 1 antibody (anti‐PD‐L1) and platinum‐etoposide is the current standard first‐line treatment for patients with extensive‐stage (ES) small cell lung cancer (SCLC). However, the best treatment for relapsed ES‐SCLC after the first‐line treatment remains unclear. There are some approved chemotherapeutic agents that can be used against ES‐SCLC, and treatment with irinotecan is well established as both a monotherapy and a combined therapy, in combination with platinum. Therefore, we conduct a phase II study with irinotecan in the second‐ or later‐line setting for patients with ES‐SCLC who have been previously treated with combined treatment.

**Methods:**

Our study will enroll total 30 patients who are diagnosed with ES‐SCLC and have experienced disease progression after the combined treatment. Patients will receive irinotecan on days 1, 8, and 15, which will be repeated every 4 weeks. Doses of irinotecan (100/80/60 mg/m^2^) will be determined according to the type of UGT1A1 gene polymorphism, and the treatment will be discontinued following disease progression, intolerance, withdrawal of patient consent, and based on the investigator's decision. The primary endpoint of the study is the response rate, and the secondary endpoints are overall survival, progression‐free survival, and safety.

**Discussion:**

Since the present first‐line treatment has been changed to the combined treatment, the second‐ or later‐line treatment should be re‐evaluated for patients with relapsed SCLC. Irinotecan is a major chemotherapeutic agent used for SCLC. This study demonstrates and re‐evaluates the clinical benefits of irinotecan after combined treatment with anti‐PD‐L1 and platinum‐etoposide for patients with ES‐SCLC.

**Registration details:**

This study was registered in the Japan Registry of Clinical Trials (no. jRCT s071210090) on November 4, 2021.

## INTRODUCTION

Small cell lung cancer (SCLC) accounts for approximately 15% of all lung cancers and tends to progress and disseminate rapidly, resulting in 70%–85% of patients being diagnosed with extensive‐stage (ES)‐SCLC, defined as the presence of metastatic lesions outside the hemithorax at the time of diagnosis.^1^, ^2^, ^3^, ^4^ Representative first‐line treatment for patients with ES‐SCLC consists of platinum and etoposide or irinotecan therapy;^5^, ^6^ however, two recent clinical trials have revealed that the addition of anti‐programmed death‐ligand 1 antibody (anti‐PD‐L1) to platinum‐etoposide therapy statistically prolonged progression‐free survival (PFS) compared to that with platinum‐etoposide therapy. Therefore, combined treatment using anti‐PD‐L1 and platinum‐etoposide is now the standard treatment in the first‐line setting for patients with ES‐SCLC.^7^, ^8^ Although treatment with anti‐PD‐L1 plus platinum‐etoposide remarkably yields a high response rate and clinical benefits, almost all patients experience relapse and acquire resistance to the treatment, suggesting the importance of the strategies in the second‐ or later‐line setting.

In cases of relapse after platinum‐etoposide treatment, the standard treatment includes a regimen identical to the initial therapy, nogitecan monotherapy,^9^, ^10^ cisplatin + etoposide + irinotecan combined therapy,^11^ and amrubicin (AMR) monotherapy.^12^, ^13^, ^14^ While these treatments demonstrate certain antitumor effects in patients with ES‐SCLC, the survival benefits are not sufficient. Furthermore, the best treatment for relapsed ES‐SCLC after first‐line combined chemo‐immunotherapy remains unclear.

Treatment with irinotecan for patients with ES‐SCLC is well established as both a monotherapy and that in combination with platinum.^5^, ^15^ Irinotecan is directly converted to its active metabolite, SN‐38, by carboxylesterase, primarily in the liver. SN‐38 is glucuronidated by UDP‐glucuronyltransferase (UGT) 1A1, a hepatic metabolic enzyme, to form an SN‐38 glucuronide conjugate (SN‐38G), which is mainly excreted in the bile. The *UGT1A1* gene is genetically polymorphic, and individuals who are heterozygous or homozygous for *UGT1A1*6* and *UGT1A1*28* have reduced ability to produce SN‐38G and delayed SN‐38 metabolism compared to that of the wild‐type.^16^ As a result, the incidence of grade 3 or higher neutropenia and diarrhea is higher in patients with the *UGT1A1* polymorphism. Although irinotecan therapy has been approved in many countries as a SCLC treatment, the effect of irinotecan after combined treatment with anti‐PD‐L1 and platinum‐etoposide remains unelucidated.

Our study is a phase II trial on irinotecan in the second‐ or later‐line setting after combined treatment with anti‐PD‐L1 and platinum‐etoposide against ES‐SCLC to evaluate the effect of irinotecan after treatment with anti‐PD‐L1 plus platinum‐etoposide. We will evaluate the suitability of irinotecan dosage according to the *UGT1A1* status after treatment with anti‐PD‐L1 and platinum‐etoposide.

## METHODS

### Study design

This is a multicenter, single‐arm, phase II study evaluating the efficacy and safety of investigational therapy (single‐agent irinotecan) in recurrent SCLC after treatment with anti‐PD‐L1 and platinum‐etoposide (Figure. 1). We will enroll 30 patients diagnosed with ES‐SCLC who experience disease progression after anti‐PD‐L1 and platinum‐etoposide. The overall response rate (ORR) is 44% for sensitive relapse SCLC with amrubicin 40 mg/m^2^ treatment,^13^ and 31.1% for refractory relapse SCLC with amrubicin 40 mg/m^2^ treatment.^17^ The ORR is 13% for SCLC with topotecan 1 mg/m^2^ treatment.^12^ Since 35 mg/m^2^ is often used in clinical practice and refractory relapse was included in this study, assuming an overall response rate of 25% as the threshold response rate, a target response rate of 40% was established. Based on an alpha value of 0.2 and a beta of 0.8, the estimated required number of patients was 30.

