### Endpoints

The primary endpoint of the present study is the response rate, and the secondary endpoints are overall survival (OS), progression‐free survival (PFS), and safety. Efficacy will be assessed according to the Response Evaluation Criteria in Solid Tumors version 1.1. PFS is defined as the time from registration to disease progression or death from any cause, whereas OS is defined as the time from registration to the last day confirmed to be alive or dead from any cause. The Kaplan–Meier method will be used to estimate PFS and OS. Survival analysis will be conducted at the end of the follow‐up period.

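### The sample-size statement labels 80% power as a beta of 0.8; the planned 30 patients fit beta 0.2 with a one-sided alpha of 0.2, so the wording is wrong but the number is not

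*Protocol article*

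**What the plan says.** The protocol article describes the trial in its Study design section: "This is a multicenter, single‐arm, phase II study". The Endpoints section gives the variable that the sample size must serve: "The primary endpoint of the present study is the response rate". The two response rates are in Study design: "assuming an overall response rate of 25% as the threshold response rate", and "a target response rate of 40% was established". The error rates and the resulting sample size follow in one sentence: "Based on an alpha value of 0.2 and a beta of 0.8, the estimated required number of patients was 30".

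The article gives no other error rate for the primary endpoint. It does not say whether alpha is one- or two-sided, which test was used, or how many responses would count as success.

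**The concern.** By standard definition beta is the probability of missing a treatment that truly reaches the target, and power is 1 − beta. Read literally, "Based on an alpha value of 0.2 and a beta of 0.8" describes a trial that would miss a true 40% response rate four times in five. The literal pair is also degenerate under a one-sided reading. Power is 1 − 0.8 = 0.2, the same as alpha, and a rule that declares success at random one time in five has those error rates without any patients.

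The Discussion makes the case for irinotecan depend on the primary endpoint being met. The error rates tell a reader what meeting it would be worth, so the one sentence that gives them should be correct.

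**Working it through.** **Inputs, all from Study design.** Threshold p0 = 0.25; target p1 = 0.40; alpha = 0.2; the second figure 0.8, printed as beta; stated n = 30. Sidedness is not given, so both readings are tried.

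**Method.** X is the number of responders among n. For each n, take the smallest cut-off r with P(X ≥ r | n, p0) ≤ the allowed upper-tail error. Power is then P(X ≥ r | n, p1). The required n is the first one at which power reaches its requirement.

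**1. Reproducing the stated 30: 0.8 read as power, alpha 0.2 one-sided.**

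| n | r | P(X ≥ r \| 0.25) | P(X ≥ r \| 0.40) |
|---|---|---|---|
| 28 | 10 | 0.1385 | 0.7412 |
| 29 | 10 | 0.1663 | 0.7853 |
| **30** | **10** | **0.1966** | **0.8237** |

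The first n with power of at least 0.80 is 30. Its actual beta is 1 − 0.8237 = 0.176.

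**2. The sentence as printed: beta 0.8, so power 0.2.**

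- Alpha 0.2 one-sided: n = 3, r = 2. Under p0: 3 × 0.25² × 0.75 + 0.25³ = 0.1406 + 0.0156 = 0.156. Under p1: 3 × 0.40² × 0.60 + 0.40³ = 0.288 + 0.064 = 0.352.
- Alpha 0.2 two-sided (0.1 in the upper tail): n = 7, r = 4, with upper-tail error 0.071 and power 0.290.
- Because exact power moves in a saw-tooth, one may require it to hold for every larger n as well. That gives 5 and 9.
- Normal and arcsine approximations give at most 6.

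None is near 30.

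**3. Could a beta of 0.8 hold at n = 30 with some other cut-off?** At r = 14, type I error is 0.0082 and beta is 1 − 0.2855 = 0.715. At r = 15, they are 0.0027 and 1 − 0.1754 = 0.825. A beta near 0.8 at n = 30 thus goes with a type I error well below 0.01, not 0.2.

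**4. Power 0.8 with alpha 0.2 two-sided.** The exact test first reaches 80% at n = 46 (r = 16, upper-tail error 0.0896, power 0.8078). At n = 30 the cut-off would be 12 (upper-tail error 0.0507, power 0.569). A cut-off of 11 has power 0.709, but its upper-tail error is 0.1057, just above 0.1. This reading does not give 30.

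**5. Does the match depend on the exact test?** The normal approximation for power 0.8 and one-sided alpha 0.2, with z = 0.8416 for both, is

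n = [(0.8416 × √(0.25 × 0.75) + 0.8416 × √(0.40 × 0.60)) / 0.15]² = [0.8416 × (0.4330 + 0.4899) / 0.15]² = 26.8, so 27.

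Other approximations with the same inputs give 24 (variance at p0), 28 (arcsine), 31 (variance at p1; 30.2 before rounding up) and 34 (continuity-corrected). With alpha two-sided, the same five formulas give 38 to 49. The stated 30 therefore points to power 0.8 and a one-sided alpha. It does not by itself prove which test was used.

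**The case against.** The strongest reply is that no numeral in the sentence is wrong. The figures 0.2, 0.8, 25% and 40% give exactly 30 once 0.8 is taken as power, and any statistician would read it so, since 20% power would need fewer than ten patients. That stands, and it limits the point to a mislabelled error rate.

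A reader might infer more from the printed words: that the trial has 20% power, or that 30 patients cannot be justified. The documents do not support either. The stated sample size rules out the 20% reading, and the apparently intended calculation reproduces 30.

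A reader might also treat the unstated sidedness as a fault in its own right, and cite power of 0.569 or a need for 46 patients. That does not stand either. A condensed article may leave sidedness, the test and the critical count to the full protocol, which is not shown. A threshold with a higher target is a comparison in one direction, and only the one-sided reading gives 30.

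Condensation does not excuse the label. The article chose to print the type II error rate and printed it wrongly, and no fuller document could make a beta of 0.8 consistent with 30 patients under the stated alpha and response rates.

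**Conclusion.** Wrong as written. The only type II error figure given for the primary endpoint is printed as 0.8, where the planned sample size implies a nominal 0.2 (actual value 0.176 under the exact test). The literal inputs call for about 3 to 7 patients. With power 0.8 and one-sided alpha 0.2 they call for exactly 30.

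This corrects the stated operating characteristics. It does not show an underpowered design, and the sample size does not change.

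The conclusion that beta is misprinted needs only the standard definition of beta and the four figures in Study design. The one-sided reading is an inference from the match with 30. The actual error rates of 0.197 and 0.176 also assume an exact binomial test with all 30 patients evaluable, and the article does not state that test. Whether a one-sided alpha of 0.2 is strict enough is a separate question, not judged here.

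**What to change.** Restate the error rates as: *one-sided alpha 0.2 and beta 0.2 (power 80%)*, keeping 30 patients. The sponsor should check the original calculation and confirm that alpha was one-sided.

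If that calculation was an exact binomial test, it would help to add the test and its rule: success if at least 10 of 30 respond, actual one-sided type I error 0.197, power 0.824. If another method was used, name that method and its own success rule instead.

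The cost is one sentence, with no change to enrolment or treatment.

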**FIGURE 1 tca15097-fig-0001:**
[figure not shown]
Schema of the study.

Our study is conducted in accordance with the Declaration of Helsinki and the Good Clinical Practice Guidelines and was reviewed and approved by the clinical review board of Nagasaki University (CRB21‐007‐4). All participants will provide written informed consent. The study was registered in the Japan Registry of Clinical Trials (no. jRCT 071210090) on November 4, 2021.

### Inclusion criteria

Presence of histologically or cytologically confirmed SCLC (combined SCLC is eligible).Patients with relapse after anti‐PD‐L1 and platinum‐etoposide treatment for SCLC (both sensitive and refractory relapse cases are eligible).Eastern Cooperative Oncology group performance status (PS) of 0–2.Age ≥ 20 years.No active malignancy (other than intraepithelial and intramucosal carcinoma equivalent lesions that has undergone potentially curative therapy) within the last 5 years prior to consent.Signed written informed consent.The latest laboratory results within 14 days before enrollment (the same day of the week 2 weeks before enrollment is acceptable) meet all of the following criteria: (a) neutrophil count ≥1500/μL, (b) platelet count ≥100 × 10^3^/μL, (c) total bilirubin (T‐Bil) ≤1.5 mg/dL, (d) aspartate aminotransferase (AST) ≤100 U/L, (e) alanine aminotransferase (ALT) ≤100 U/L, (f) serum creatinine (Cr) ≤1.5 mg/dL, (g) SpO_2_ on room air ≥92%.

### Exclusion criteria

Interstitial pneumonia that can be detected using chest radiographs.Chest radiation treatment within 28 days.Superior vena cava syndrome that requires urgent radiation therapy.Clinically serious cardiac disease such as angina pectoris, uncontrolled heart failure, or myocardial infarction within 3 months.Uncontrolled diabetes mellitus.Uncontrolled hypertension.Active systemic infection that requires treatment.Pregnant, or possibly pregnant, postpartum in 28 days, breastfeeding.Fever of ≥38.0°C.Mental disorder or symptoms interfering with daily life and inappropriate for enrollment.Receiving continuous systemic administration (oral or intravenous) of steroids or immunosuppressive drugs equivalent to 11 mg/day or more of prednisolone.Positive for hepatitis B surface antigen.Positive for human immunodeficiency virus antibody (not necessarily examined).Other inappropriate complications.

### Interventions

Patients will receive irinotecan on days 1, 8, and 15, which will be repeated every 4 weeks. Doses of irinotecan will be determined according to the type of *UGT1A1* gene polymorphism (wild type: 100 mg/m^2^, *6/− or *28/−: 80 mg/m^2^, *6/*6, *28/*28 or *6/*28: 60 mg/m^2^), and treatment will be continued until disease progression, intolerance is detected, or the patient withdraws consent, and based on the investigator's decision.

### Endpoints

The primary endpoint of the present study is the response rate, and the secondary endpoints are overall survival (OS), progression‐free survival (PFS), and safety. Efficacy will be assessed according to the Response Evaluation Criteria in Solid Tumors version 1.1. PFS is defined as the time from registration to disease progression or death from any cause, whereas OS is defined as the time from registration to the last day confirmed to be alive or dead from any cause. The Kaplan–Meier method will be used to estimate PFS and OS. Survival analysis will be conducted at the end of the follow‐up period.

## DISCUSSION

To our knowledge, this is the first prospective study to evaluate the effect of irinotecan after combined therapy of anti‐PD‐L1 and platinum‐etoposide. Our study will provide a convincing option of irinotecan therapy after anti‐PD‐L1 and platinum‐etoposide therapy in treating SCLC if the primary endpoint is achieved.

In our previous study, the sequence of chemotherapy following nivolumab in non‐small cell lung cancer enhanced the antitumor activity of cytotoxic chemotherapy.^18^ In addition, a recent retrospective study revealed that the efficacy of AMR therapy after chemo‐immunotherapy in patients with SCLC showed an overall response rate of 47% (95% confidence interval [CI]: 30%–64%), and the disease‐control rate of 73% (95% CI: 56%–86%),^19^ indicating that single agent of AMR is a useful treatment option after chemo‐immunotherapy. Irinotecan is a topoisomerase I inhibitor and a major chemotherapeutic agent and has been used for treating SCLC for a long time. The response rates of 47% in 16 previously treated SCLC patients^15^ and 79% in untreated patients with advanced SCLC in combination with cisplatin^20^ have been reported. Furthermore, sequential administration of topoisomerase I inhibitors (irinotecan and nogitecan) and topoisomerase II inhibitors (etoposide and AMR) have been suggested to show clinical benefits.^21^ The current standard first‐line treatment includes anti‐PD‐L1, cisplatin, topoisomerase II inhibitor (etoposide); therefore, this study may provide valuable results for treating patients with SCLC.

Consistent with the significant associations between the UGT1A1*6 genotype and irinotecan‐induced toxicities in Asian populations, the Japanese Pharmaceuticals and Medical Devices Agency recommends screening patients for UGT1A1*6 and *28 polymorphisms. The US Food and Drug Administration also recommends a reduction in the irinotecan starting dose in patients who are homozygous for UGT1A1*28.^16^ Therefore, we aim to adjust the irinotecan dose according to the UGT1A1 type and demonstrate that irinotecan can be safely administered even in patients with UGT1A1*6 and UGT1A1*28 genotypes.

In conclusion, our study will demonstrate and re‐evaluate the efficacy and safety of irinotecan after combined treatment with anti‐PD‐L1 and platinum‐etoposide for patients with ES‐SCLC.

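### With 30 patients sized on response alone, the trial cannot demonstrate that irinotecan is safe in patients with two UGT1A1 variant alleles; safety by genotype should be called descriptive.

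*Protocol article*

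**What the plan says.** Two places state a purpose tied to genotype. The Introduction says "We will evaluate the suitability of irinotecan dosage according to the *UGT1A1* status after treatment with" the first-line combination. The Discussion goes further and states the aim to "demonstrate that irinotecan can be safely administered even in patients with UGT1A1*6 and UGT1A1*28 genotypes".

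The design behind these aims is as follows.

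- Interventions: "Doses of irinotecan will be determined according to the type of *UGT1A1* gene polymorphism", which gives three genotype-dose groups: no variant allele, one variant allele, and two variant alleles (\*6/\*6, \*28/\*28 or \*6/\*28).
- Study design: the number of patients comes from response only. The article says "assuming an overall response rate of 25% as the threshold response rate, a target response rate of 40% was established", and then "Based on an alpha value of 0.2 and a beta of 0.8, the estimated required number of patients was 30".
- Endpoints: response rate is primary, and "the secondary endpoints are overall survival (OS), progression‐free survival (PFS), and safety".

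The article gives no toxicity rate that the trial is meant to exclude, no genotype frequency and no expected number per genotype group. The Introduction does say that grade 3 or higher neutropenia and diarrhoea occur more often in patients with the polymorphism.

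**The concern.** To demonstrate safety is to exclude an unacceptable rate of severe toxicity with reasonable confidence. That needs a rate to exclude and enough patients to exclude it. The article states neither for carriers, and its only sample size argument concerns response in all 30 patients together.

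The difficulty is greatest in the two-allele group, which is likely to be the smallest. A handful of patients with few or no severe events is a likely result even when the true rate is substantial. Under the stated aim, such a result could be reported as showing safety in patients whom the article itself describes as more prone to severe neutropenia and diarrhoea.

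**Working it through.** **Step 1: the plan's own figure.** Inputs from Study design: threshold 25%, target 40%, alpha 0.2, and 0.8, which has to be read as power. An exact one-sample binomial test at one-sided alpha 0.20 with at least 80% power has a smallest n of 30, with success at 10 or more responses:

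- P(X ≥ 10 | n = 30, p = 0.25) = 0.1966
- P(X ≥ 10 | n = 30, p = 0.40) = 0.8237

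So 30 is fully explained by the response test, and neither toxicity nor genotype enters it.

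**Step 2: likely group sizes (an assumption).** The article gives no frequencies. Let q be the combined frequency of the two variant alleles. Under Hardy-Weinberg proportions the expected numbers among 30 are 30(1−q)² with no variant allele, 30·2q(1−q) with one and 30q² with two.

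| q | no variant | one allele | two alleles | all carriers |
|---|---|---|---|---|
| 0.20 | 19.2 | 9.6 | 1.2 | 10.8 |
| 0.30 | 14.7 | 12.6 | 2.7 | 15.3 |
| 0.40 | 10.8 | 14.4 | 4.8 | 19.2 |

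This gives about 1 to 5 patients with two alleles, 10 to 14 with one, and 11 to 19 carriers in all. An equal split of 10 per group is added as a case generous to the two-allele group.

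**Step 3: what no severe events would show.** With zero events in n patients the exact (Clopper-Pearson) two-sided 95% upper limit is 1 − 0.025^(1/n).

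| group | n | upper limit |
|---|---|---|
| two alleles | 1 | 97.5% |
| two alleles | 2 | 84% |
| two alleles | 3 | 71% |
| two alleles | 5 | 52% |
| two alleles, equal split | 10 | 31% |
| one allele | 10 to 14 | 31% to 23% |
| all carriers | 11 to 19 | 28% to 18% |

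Conversely, a true rate of 30% would produce no event in 3 patients with probability 0.7³ = 0.343.

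**Step 4: what some events would show.** With x events the upper limit is the 97.5% point of a Beta(x + 1, n − x) distribution.

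- Two alleles: 1/3 gives 91%, 1/5 gives 72%.
- One allele: 3/10 gives 65%, 3/14 gives 51%.
- All carriers: 3/15 gives 48%, 6/15 gives 68%.

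**Step 5: numbers that would be needed.** The number of event-free patients for a two-sided 95% upper limit at or below a rate t is the smallest n with (1 − t)^n ≤ 0.025:

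- t = 50%: 6 patients
- t = 40%: 8
- t = 30%: 11
- t = 20%: 17
- t = 10%: 36, more than the whole trial

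**Step 6: chance of success in a larger group.** If the true rate is 20%, the probability that a one-sided 95% limit falls below 40% is 0 with 3 or 5 patients, 0.38 with 10, 0.28 with 12 and 0.40 with 15. It is not monotone because the counts are discrete.

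**The case against.** The strongest reply is that this is one verb in a Discussion. The Introduction uses a softer one, safety is only a secondary endpoint, no hypothesis or success rule is attached to it, and the article uses the same verb loosely elsewhere. All of that is true. It means that the primary analysis is untouched and that no decision rule in the plan would produce a false declaration of safety. It does not remove the stated aim, which names the genotypes and claims more than the design can deliver.

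Three stronger readings are tempting, and the document does not support them.

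- A reader might infer that the trial has too few carriers of any kind to exclude even very high toxicity rates. That holds only for the two-allele group. With no events, the one-allele group and the pooled carriers would exclude rates above roughly 31% to 23% and 28% to 18%. With more events the limits rise, so the answer depends on the data.
- A reader might infer that safety will be analysed only for all patients together. The Endpoints section names safety without saying how it is broken down, and the Introduction points towards an analysis by genotype.
- A reader might infer that a safety table by genotype has been forgotten. A condensed article may leave that to the full protocol or the analysis plan, so its absence is no fault. Those documents could add a table, but a table cannot make 1 to 5 patients sufficient.

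The group sizes are assumed. The conclusion for the two-allele group does not hinge on them closely: with 10 patients and no event, 31% remains possible.

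**Conclusion.** The point holds for the two-allele group. Across the assumed allele frequencies, the best possible result there, no severe event at all, leaves true rates above 50% open. The article offers no ground for expecting so clean a result, since it reports more severe toxicity in carriers and states no expected rate at the assigned doses.

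For one-allele and pooled carriers the narrower statement is that the trial was not sized for a safety conclusion and states no limit against which to judge one. What it can exclude there depends on the number of events.

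This is an overstated aim with a modest remedy. It does not affect the response-rate test. It rests on the assumed allele frequency of 0.20 to 0.40, on Hardy-Weinberg proportions, and on exact 95% limits as the standard of evidence.

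**What to change.** 1. In the Discussion, replace the aim of demonstrating safe administration in carriers with the aim of describing the safety of irinotecan by UGT1A1 genotype group.
2. Report grade 3 or higher neutropenia and diarrhoea for each of the three groups, as counts with exact 95% confidence intervals. This gives the reworded aim its content.
3. State that no safety conclusion will be drawn for the two-allele group from this trial alone.

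The cost is a change of wording and one table. Genotype is already known for every patient because it sets the dose. The drawback is a weaker safety claim. No dose, schedule or sample size changes.
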